### Statistical method

2.9

This study will analyze data based on the intention-to-treat (ITT) principle. Efficacy will be evaluated based on the full analysis set (FAS), and safety will be evaluated based on the safety analysis set (SS). FAS is defined as all participants who were randomly assigned, received at least one dose of the study drug, and have efficacy evaluations. The safety analysis set is defined as all participants who were randomly assigned, received at least one dose of the study drug, and have safety assessments, summarized by the actual treatment received.

The primary endpoint, the change in QMG score from baseline at 30 weeks, will be compared using ANCOVA for E + 1w+T vs. T only and E + 2w+T vs. T only, adjusting for baseline QMG score. Missing values for the primary endpoint will be handled using the last observation carried forward (LOCF) method. Secondary endpoints will be analyzed according to general statistical principles. Two-sided tests will be used with a significance level of 5%.

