**Figure 1 f1:**
[figure not shown]
Study flowchart. MG, myasthenia gravis.

E+1w+T group: Participants will receive efgartigimod induction therapy at 10 mg/kg, administered via intravenous infusion over 1 hour, once weekly for a total of 4 consecutive doses (Weeks 0–3). One week after completing induction therapy, telitacicept maintenance therapy will be initiated at a dose of 240 mg, administered subcutaneously once weekly from Week 4 for a total of 25 weeks. Participants will be followed until Week 30.

E+2w+T group: Participants will receive efgartigimod induction therapy at 10 mg/kg via intravenous infusion, once weekly for a total of 4 consecutive doses (Weeks 0–3), as in the E + 1w+T group. However, telitacicept maintenance therapy (240 mg, subcutaneously once weekly) will be initiated two weeks after completing induction therapy, starting from Week 5, and will continue for 24 weeks. Participants will be followed until Week 30.

T only group: Participants will not receive efgartigimod induction therapy. Instead, they will receive telitacicept 240 mg subcutaneously once weekly from Week 0 for a total of 30 weeks. Participants will be followed until Week 30.

From Week 8 to Week 30, if the patient reaches the Minimal Symptom Expression (MSE) criterion (MG-ADL ≤ 1) or experiences significant improvement in the Post-Intervention Status (PIS), or if the investigator deems dose reduction necessary, a reduction in the standard treatment is allowed. The recommended sequence for dose reduction is to first reduce or discontinue pyridostigmine bromide, followed by a reduction or discontinuation of non-steroidal immunosuppressive agents (e.g., tacrolimus, azathioprine, mycophenolate mofetil), and finally a reduction or discontinuation of corticosteroids. However, this order may be adapted at the discretion of the investigator based on the patient’s clinical condition, medication tolerance, and treatment response. To ensure stable disease control, a 2–4 week interval should be observed between the reduction or discontinuation of each class of medication. If disease exacerbation occurs during the study (MG-ADL increase≥2 points), but the patient does not reach a crisis state, an increase in the standard treatment or the use of a rescue regimen is permitted.

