### Endpoints

2.6

The primary endpoint is the change from baseline in the QMG score at Week 30 after randomization. Secondary endpoints include the assessment of the following variables at Weeks 4, 8, 12, 18, 24, and 30 after randomization: change from baseline in the MG-ADL score; the proportion of patients achieving minimal manifestation status (MMS) (defined as the absence of any functional limitations due to myasthenia, with certain weakness detected by a trained neurologist); the proportion of patients with a reduction of ≥2 points in the MG-ADL score from baseline; the proportion of patients with a reduction of ≥3 points in the QMG score from baseline; changes in the dose of corticosteroids and other immunosuppressive agents at Weeks 24 and 30; the proportion of patients who discontinue corticosteroids and other immunosuppressive agents at Weeks 24 and 30; the proportion of patients on prednisone (or equivalent corticosteroids) ≤5 mg/day at Weeks 24 and 30; the incidence of MG relapse/acute exacerbation and MG crisis at Week 30; and the incidence of AEs and SAEs.

The study will also analyze the PK/PD characteristics of telitacicept in different sequential treatment groups. Blood samples will be collected to measure PK-related indicators before the first administration of telitacicept (30 minutes prior), and at 6, 24, 48, and 72 hours, as well as at Week 1, 4, 8, 12, and 24 (before each dose). The PK parameters to be measured include blood drug concentration, clearance rate, volume of distribution, interindividual variability, and other relevant indicators. Immune globulins will be tested during the screening period, during the first cycle of efgartigimod treatment, prior to the first dose of telitacicept, and at Weeks 1, 4, 8, 12, and every 4 weeks thereafter, until the end of the study. During the screening period, prior to the first dose of telitacicept, and at Weeks 4, 12, and 24 of telitacicept treatment, BLyS/APRIL, B-cell flow cytometry, T-cell flow cytometry, and cytokines such as IL-6 will be assessed, all before dosing.

The evaluation of adverse events will adhere to the NCI-CTCAE V5.0.

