In the efgartigimod phase 3 clinical trial and the extended observation ADAPT+ study, patients showed a rebound in disease scores, such as MG-ADL and QMG, 2 weeks after completing one treatment cycle, with scores returning to baseline levels 4–5 weeks after discontinuation (10). A multicenter, randomized, open-label phase 2 clinical trial of telitacicept in patients with gMG indicated that the efficacy of telitacicept is significant after 4 weeks of administration (15). Therefore, in this study, the initiation of telitacicept in one sequential treatment group will be set to 1 week after efgartigimod discontinuation to avoid symptom rebound due to prolonged treatment gaps. Considering the theoretical degradation effect of efgartigimod on the IgG Fc fusion protein in telitacicept, the other sequential treatment group will begin telitacicept treatment 2 weeks after efgartigimod administration, following 3 half-lives of efgartigimod (13), to avoid the influence of residual drug concentrations on subsequent treatment while stabilizing patients’ symptoms as far as possible. The study will compare two sequential treatment groups with different time intervals, conducting a multidimensional assessment of efficacy, safety, and PK/PD characteristics to explore the optimal sequential treatment strategy.

This study is the first clinical trial to explore sequential treatment strategies for gMG. One of the strengths of this study is its randomized, parallel-controlled design. Another advantage is the inclusion of PK/PD assessments, in addition to efficacy and safety data. The design of the PD indicators is based on the pharmacological mechanisms of efgartigimod and telitacicept, including immunoglobulin, B cell count, and/or BLyS+APRIL levels. Efgartigimod promotes IgG clearance (18), while telitacicept, a dual inhibitor of BLyS/APRIL, inhibits B cell maturation and suppresses the secretion of autoantibodies by blocking BLyS and APRIL (16). Monitoring these relevant PD indicators allows the study to analyze the rationale behind the sequential treatment strategy from a pharmacodynamic perspective.

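### Carrying the last QMG score forward to Week 30 can bias both sequential-versus-monotherapy comparisons, in either direction, because the arms improve on different timetables

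*Protocol article*

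**What the plan says.** Endpoints (2.6) defines the target: "The primary endpoint is the change from baseline in the QMG score at Week 30 after randomization". Statistical method (2.9) says that it "will be compared using ANCOVA for E + 1w+T vs. T only and E + 2w+T vs. T only, adjusting for baseline QMG score". For a missing Week-30 score it names one rule: "Missing values for the primary endpoint will be handled using the last observation carried forward (LOCF) method".

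The scores that could be carried come from the visit schedule in Endpoints: "Secondary endpoints include the assessment of the following variables at Weeks 4, 8, 12, 18, 24, and 30 after randomization". QMG must be scored at these visits because the list includes "the proportion of patients with a reduction of ≥3 points in the QMG score from baseline".

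The article describes the time courses as follows:

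- Both sequential arms receive efgartigimod "once weekly for a total of 4 consecutive doses (Weeks 0–3). One week after completing induction therapy", telitacicept starts in the first of them (Week 4). In the second it starts at Week 5. The monotherapy arm has telitacicept from Week 0 (Randomization and intervention, 2.3).
- After an efgartigimod cycle, the Discussion reports a rebound at 2 weeks, "with scores returning to baseline levels 4–5 weeks after discontinuation".
- For telitacicept, the Discussion says that "the efficacy of telitacicept is significant after 4 weeks of administration".

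Criteria for discontinuing (2.5) lists rescue treatment, and an investigator's view that the patient is not benefiting, among the grounds for ending participation.

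**The concern.** Last observation carried forward gives a valid Week-30 comparison only if the arm difference at the last visit equals the arm difference at Week 30 among those who leave. The article's pharmacology argues against that.

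The Week-4 visit falls one week after the last infusion, before the described rebound. A sequential-arm participant last seen then carries a short-lived benefit forward 26 weeks. A monotherapy participant last seen at Week 4 carries a score from about the time telitacicept starts to work. By the Week-8 visit the picture may reverse: the efgartigimod effect should have worn off and the sequential arms are only 3 to 4 weeks into telitacicept, while the monotherapy arm is 8 weeks in.

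The distortion comes from the regimens, so equal dropout in the arms does not cancel it. Durability after induction is what the trial sets out to test, and the imputation rule assumes it for everyone who leaves. Some exits will also be related to outcome, because rescue and lack of benefit can end participation.

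**Working it through.** **The plan's own figure.** Sample size calculation (2.7) gives a 4-point difference, SD 4.3, R² 0.3, two-sided α 0.025, 80% power and 15% dropout. The adjusted SD is 4.3 × √0.7 = 3.60. The noncentral-t ANCOVA calculation (df = 2n - 3) gives 77.8% power at n = 16 and 80.7% at n = 17, so 17 per group. Then 17 / 0.85 = 20. The planned numbers reproduce.

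**Formula.** Let D be the mean QMG change in a sequential arm minus that in monotherapy, so negative values favour sequential therapy. Let d be the share with Week 30 missing, equal in both arms.

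bias = d × (D at last visit - D at Week 30)

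The article gives no visit-by-arm means and no dropout timing. The values of D at the last visit below are assumptions, shown as a range.

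**No true Week-30 difference, d = 0.15:**

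| D at last visit | Bias (points) | Favours |
|---|---|---|
| -6 | 0.15 × (-6) = -0.9 | sequential |
| -5 | -0.75 | sequential |
| -4 | -0.6 | sequential |
| -2 | -0.3 | sequential |
| +2 | +0.3 | monotherapy |
| +4 | +0.6 | monotherapy |

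**False positives in favour of sequential therapy (two-sided 5% test, nominal 2.5%).**

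- *All exits after Week 4.* Assume Week-4 means of -8 (sequential) and -3 (monotherapy), and -9.6 in both arms at Week 30. Carried values also widen the spread within an arm, by d(1 - d) × (gap between Week-4 and Week-30 means)². The adjusted variances are 12.94 + 0.1275 × 1.6² = 13.27 and 12.94 + 0.1275 × 6.6² = 18.50. The SE is √((13.27 + 18.50)/20) = 1.26, and the bias is -0.75/1.26 = -0.60 SE. This gives about 8%, and simulations of the ANCOVA gave 7.5% to 8.1%. With -6 against -3 the bias is -0.45 and the rate about 5%.
- *Exits spread evenly over the five visits, same Week-4 gap, no later gap.* One fifth of the 15% leave after Week 4, so the bias is 0.03 × (-5) = -0.15. With SE 3.60 × √(2/20) = 1.14, the normal approximation gives Φ(-1.96 + 0.15/1.14) = 3.4%.

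**How timing sets the sign.** Assume monotherapy means of -3, -6, -7.5, -8.8, -9.6 at Weeks 4, 8, 12, 18, 24, and sequential means with a rebound trough of -6, -1.5, -5, -7.5, -9, with both at -9.6 at Week 30.

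- All exits after Week 4: 0.15 × (-3) = -0.45.
- All exits after Week 8: 0.15 × (+4.5) = +0.68.
- Even spread: 0.15 × (-3 + 4.5 + 2.5 + 1.3 + 0.6)/5 = +0.18. Without a trough (a -3 gap at Week 4 only) it is 0.15 × (-3)/5 = -0.09.

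**True Week-30 difference of -4 (the design assumption), d = 0.15.** Power is for n = 20 per arm at two-sided 0.025, with a common adjusted SD of 3.60.

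| D at last visit | Bias (points) | Power |
|---|---|---|
| -6 | -0.3 | 92.0% |
| -4 | 0 | 87.6% |
| -2 | +0.3 | 81.6% |
| 0 | +0.6 | 74.1% |

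**The case against.** A reader might infer that the rule always favours sequential therapy. The documents do not support that. The sign needs both early exits and a true difference near zero. Week-8 exits may reverse it. Under the design assumption, Week-4 means of -8 and -3 leave only 0.15 × (-5 + 4) = -0.15 points, and -6 and -3 give +0.15, against sequential therapy. This part of the objection stands.

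Two other tempting claims fail. Calling the monotherapy Week-4 score pre-onset is too strong, since the Discussion puts onset at about 4 weeks. Nor is there evidence here that the standard error alone corrupts the test: with equal Week-4 means, simulated favourable rejection was 2.4% against a nominal 2.5%.

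It is also fair to say that the trial is labelled exploratory, that about 3 participants per arm are affected at the planned dropout, and that sensitivity analyses may sit in an analysis plan that is not shown. Their absence is not part of this point. A repeated-measures model has its own assumption, too: it treats someone who left at Week 4 like arm-mates who continued, which may not hold for exits after rescue.

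None of this rescues the stated rule. It is an explicit choice for the primary endpoint, and the article's own time courses contradict its premise.

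**Conclusion.** The point holds in two-directional form. The carried score misstates Week 30 by an amount that differs by arm, and the sign and size depend on when participants leave and on the true effect.

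With no true difference, 15% dropout and 20 per arm, the bias is 0.15 times the arm difference at the last visit. An assumed 5-point Week-4 gap gives about -0.75 points, 19% of the planned 4, if all exits follow Week 4. That is the adverse end of the range. With evenly spread exits and no later gap it falls to about -0.15 points, and it turns positive if exits cluster in a rebound trough. If the planned 4-point benefit is real, a carried difference below 4 points dilutes it.

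These sizes rest on assumed visit means and exit timing, equal dropout in both arms and exits unrelated to outcome. The finding that the rule does not suit these regimens rests only on what the article says.

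**What to change.** Replace the imputation sentence in Statistical method (2.9) with the following:

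- **Primary analysis:** a likelihood-based repeated-measures model of QMG change at Weeks 4, 8, 12, 18, 24 and 30, with arm by visit and baseline QMG by visit, and a pre-specified simpler covariance as fallback if the model does not converge with 60 participants. The two Week-30 contrasts against monotherapy are primary. Multiple imputation followed by the planned ANCOVA is an acceptable alternative.
- **Assumption:** state that this takes scores as missing at random, and so estimates the Week-30 outcome as if leavers had behaved like arm-mates who stayed.
- **Sensitivity:** one analysis that imputes unfavourably for participants who left after rescue or for lack of benefit, for example a change of zero.
- **Last observation carried forward:** supportive at most.

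The cost is a little more analysis work. The QMG scores are already collected at these visits, and the sample size stays at 20 per group. Trial status (3.1) reports that nobody had been enrolled, so the change could be made before any outcome data exist.

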### Sample size calculation

2.7

Based on previous studies (15), the change in QMG score from baseline at 24 weeks in the monotherapy group was -9.6 (± 4.3). It is assumed that the efficacy of the two sequential treatment regimens in this study will be similar, with a predicted additional 4-point reduction in the QMG score at 30 weeks for the sequential treatment group compared to the monotherapy group (10, 19), with SD = 4.3. Using a two-sided test, α = 0.025, and power = 80%, ANCOVA will be used for pairwise comparisons, assuming R2 = 0.3. The required sample size per group is 17 participants. Considering a 15% dropout rate, 20 participants per group are planned, for a total of 60 participants.

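### The two primary comparisons are sized at two-sided 0.025 each, but the analysis section gives one unqualified 5% level and does not say whether it applies to each comparison or overall

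*Protocol article*

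**What the plan says.** Section 2.7 (Sample size calculation) sets the level, the power and the model together: "Using a two-sided test, α = 0.025, and power = 80%, ANCOVA will be used for pairwise comparisons, assuming R2 = 0.3". The effect is a "predicted additional 4-point reduction in the QMG score at 30 weeks for the sequential treatment group compared to the monotherapy group", with an SD of 4.3. The result is stated as "The required sample size per group is 17 participants", raised to 20 for dropout.

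Section 2.9 (Statistical method) defines the primary analysis. The change in QMG at week 30 "will be compared using ANCOVA for E + 1w+T vs. T only and E + 2w+T vs. T only, adjusting for baseline QMG score". After a sentence on missing data and one on the secondary endpoints, the paragraph ends: "Two-sided tests will be used with a significance level of 5"%.

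Section 2.9 does not refer to 0.025, and section 2.7 does not refer to 5%. Nothing elsewhere in the article connects the two levels.

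**The concern.** Two regimens are compared with one control, so there are two chances of a positive primary result. Section 2.7 appears to allow for this: 0.025 is 0.05 divided by the two comparisons. Section 2.9 is where an analyst would look for the decision rule, and it gives only 5%.

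Two things are at stake. First, if 5% is applied to each comparison, the false-positive protection that the sample size was calculated to provide is largely lost. Second, the rule for a positive primary result is not fixed. A regimen with p = 0.03 would be positive under 2.9 read literally and not positive under 2.7. The article's Introduction says that the trial aims to define an optimal sequencing strategy, so which regimen is declared better than monotherapy is a central result. The rule should not be left to be chosen once p-values are known.

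**Working it through.** **Inputs.** From section 2.7: difference δ = 4 QMG points, SD = 4.3, R² = 0.3, two-sided α = 0.025, power 80%, 17 evaluable per group, 15% dropout. From section 2.3: 1:1:1 allocation. From section 2.9: two comparisons with a shared control, and a 5% level.

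**Step 1. Reproduce the plan's 17 per group.**
- Residual SD after baseline adjustment: 4.3 × √(1 − 0.3) = 3.60.
- Normal approximation: n = 2 × [3.60 × (z₁₋α/₂ + z₀.₈) / 4]². At two-sided 0.025, z = 2.241 + 0.842, so n = 15.4, rounded up to 16.
- Non-central t with 2n − 3 degrees of freedom (pairwise ANCOVA, one covariate): power is 77.8% at n = 16 and 80.7% at n = 17. The smallest adequate n is 17, as stated.
- Dropout: 17 / (1 − 0.15) = 20, as stated.

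**Step 2. Could 17 have come from 5%?**
- At two-sided 0.05 the normal formula gives 12.7, rounded up to 13.
- The t-based calculation gives 14 (77.5% power at 13, 80.7% at 14).
- One-sided 0.025 has the same critical value and gives the same 13 or 14.

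So 0.025 is neither a one-sided level in disguise nor a misprint for 0.05. It is the two-sided level per comparison that produces 17.

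**Step 3. Family-wise error.** With equal arms and a shared control, the two test statistics have correlation 0.5. The family-wise error is 1 − P(|Z₁| < c and |Z₂| < c) for a bivariate normal pair.

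| Level for each comparison | c | Shared control | If independent |
|---|---|---|---|
| two-sided 0.05 | 1.960 | 9.1% | 1 − 0.95² = 9.75% |
| two-sided 0.025 | 2.241 | 4.6% | 1 − 0.975² = 4.94% |

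A simulation with pairwise t tests (200,000 replicates) agrees: 9.0% and 4.6%, both at 17 and at 20 per arm.

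**Step 4. What the gap means in QMG points.** At 17 per group the standard error of a difference is 3.60 × √(2/17) = 1.234. The critical t on 31 degrees of freedom is 2.356 at 0.025 and 2.040 at 0.05.
- At 0.025: 2.356 × 1.234 = 2.9 points.
- At 0.05: 2.040 × 1.234 = 2.5 points.

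Under the planning assumptions, an observed advantage between about 2.5 and 2.9 points is positive under 2.9 read literally and not positive under 2.7.

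**Step 5. Power.** At 17 per group, power per comparison is 80.7% at 0.025 and 88.1% at 0.05. The stated 80% belongs to the 0.025 rule. Returning to that rule costs nothing against the planned power.

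**The case against.** A reader might infer that the plan commits itself to a 9% family-wise error. The text does not go that far. Section 2.9 never says that each primary comparison is tested at 5%. The sentence follows directly on the one about secondary endpoints, so 5% may be meant for those. It may also be the overall level, with section 2.7 supplying the split into two halves of 0.025. Under either reading the two sections agree and the family-wise error is 4.6%. Step 2 of the check makes an intended split more plausible. This part of the objection stands: the 9.1% is what the wording permits, not what the sponsor is shown to have chosen.

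The exploratory purpose also counts. The Abstract uses that label, and the limitations in the Discussion describe a possible proof of concept that needs larger confirmatory trials. This lowers the severity. It does not remove the conflict, because the trial still has one designated primary endpoint, a power calculation and an α that looks divided between two comparisons.

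A third objection is that a multiplicity procedure is normally left to the statistical analysis plan, which is not shown. That would answer a complaint that such a procedure is missing. It does not answer this point, which is that the article states two levels and leaves their relation open. The analysis plan can settle the matter, but section 2.9 would still need wording that agrees with it.

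Nor does the conflict mean that the trial is wrongly sized. The 17 and 20 per group follow correctly from section 2.7's own inputs.

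**Conclusion.** The point holds as an unresolved conflict between two stated levels. Section 2.7 uses two-sided 0.025 for each primary comparison; section 2.9 gives an unqualified two-sided 5% with no stated scope. Taken literally, 2.9 allows a family-wise error of about 9.1%, roughly twice the 4.6% implied by 2.7, and p-values from 0.025 to 0.05 would be judged differently.

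The error rates assume equal arms, a shared control and no true effect in either comparison. The QMG thresholds and power figures also assume the planned SD of 4.3, R² of 0.3 and 17 evaluable patients per group.

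Severity is moderate: the trial is described as exploratory, and two plausible readings of the 5% sentence remove the inflation. The primary decision rule should still be made unambiguous before data exist.

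**What to change.** In section 2.9, and in the analysis plan to match, state that each of the two primary comparisons (E+1w+T against T only, and E+2w+T against T only) is tested at two-sided 0.025, for an overall two-sided level of 5%, and that the unadjusted 5% level applies to the other tests only.

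Holm's procedure is an acceptable option, not a requirement: the smaller p-value is tested at 0.025 and, if that is significant, the other at 0.05. It also keeps the overall error at 5% and rejects whenever the fixed 0.025 rule would, but it is a rule the article does not currently contain.

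The cost is one sentence. The sample size stays at 17 evaluable and 20 randomised per group. The Trial status section reports protocol version 1.0 with nobody enrolled, so the change could be made before any data exist. The one downside is a stricter bar for the primary p-values than 2.9 read literally, and that is the bar at which the stated 80% power was calculated.
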